## Statistical design

This study is primarily designed to test for non-inferiority of outpatient recovery compared to regular treatment for bariatric surgery. The outcome measure that we will use for the analysis is a combined measure, based on the following:

- Mortality
- Severe postoperative complications (Clavien-Dindo IIIb or higher)
- Readmission (at least one night in hospital)
- Mild complications (Clavien-Dindo II and IIIa)
- Prolonged length of stay (3 days or more in hospital)

within 30 days after primary surgery.

We choose to use this combined outcome measure since it is in line with other surgical studies [5] making it comparable to literature.

I current practice at Catharina Hospital, Eindhoven, 95% of all bariatric surgery patients do not have any of these events which is considered the textbook outcome here.

We set the following null and alternative hypotheses for proving non-inferiority:

$H_0: p_{\text{regular}} - p_{\text{outpatient}} \geq \Delta$

$H_1: p_{\text{regular}} - p_{\text{outpatient}} < \Delta$

Where  $p_{\text{regular}}$  is the textbook outcome proportion in the regular treatment group, and  $p_{\text{outpatient}}$  is the textbook outcome proportion in the outpatient recovery group. We will use a non-inferiority margin ( $\Delta$ ) of 7%, which is deemed clinically significant by the Principal Investigator. This is also justified by a previous study where the average textbook outcome across bariatric surgery patients in the Netherlands was 88,7% [5] which helps to derive a non-inferiority margin of around 7% to the one seen at Catharina Hospital. We will use an uncorrected chi-squared statistic. Based on the sample size calculation done below an p value of 0.05 will be considered statistically significant. For the interim analysis an alpha correction for multiple testings is applied and a p value of 0.025 will be considered statistically significant.

The secondary endpoints will be analysed statistically in analogy to the primary endpoint by uncorrected chi-squared statistic where deemed appropriate.

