## Sample size

Sample size calculations were performed using PS: Power and Sample Size Calculation software. With a power of 0.80, an  $\alpha$  of 0.05, a non-inferiority margin of 0.07 and an expected proportion of 0.96, this resulted in a sample size of 97 (we choose 100) patients per group when using an uncorrected chi-squared statistic.

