### Pass/fail criteria

The study is considered successful if the primary endpoint is addressed and the non-inferiority of outpatient recovery compared to regular treatment for bariatric surgery can be concluded.

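### The primary test named in Section 7, an uncorrected chi-squared test at p = 0.05, tests equality of the two groups and not the 7-point non-inferiority null

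*Protocol*

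**What the plan says.** Section 7, Statistical design, introduces a margin-based framework: "We set the following null and alternative hypotheses for proving non-inferiority". H0 is that the regular-care proportion exceeds the outpatient proportion by the margin or more. H1 is that the deficit is smaller than the margin. The margin is 7 points.

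The same subsection then names the test: "We will use an uncorrected chi-squared statistic". For the final analysis, "an p value of 0.05 will be considered statistically significant"; for the interim, "a p value of 0.025 will be considered statistically significant". Neither level is given a sidedness. The same statistic is extended to the secondary endpoints by analogy.

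The Sample size subsection repeats the name. "With a power of 0.80", an alpha of 0.05, "a non-inferiority margin of 0.07 and an expected proportion of 0.96", it arrives at 97, rounded up to 100, "patients per group when using an uncorrected chi-squared statistic".

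Under Pass/fail criteria the study succeeds if the primary endpoint is addressed and "non-inferiority of outpatient recovery compared to regular treatment for bariatric surgery can be concluded".

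**The concern.** An uncorrected chi-squared statistic for two proportions is, in ordinary usage, Pearson's test without continuity correction. Its null is that the two proportions are equal, so the 7-point margin plays no part in it. A small p-value says that the groups differ, possibly because outpatients did worse. A large p-value says only that a difference was not detected, which is not evidence that the deficit is below 7 points.

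The trial's one pass/fail decision would therefore rest on a test that does not address its hypothesis. The question is one of safety: whether same-day discharge worsens a composite that includes death and severe complications. Depending on how the p-value is read, a sound pathway almost always fails, or a pathway at the unacceptable margin passes more often than not.

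**Working it through.** **Inputs.** From Section 7: margin 0.07, planning proportion 0.96 in both arms, current-practice proportion 0.95, alpha 0.05, power 0.80, 100 per group.

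**1. Reproduce the sample size.** The margin-based formula with equal true proportions at one-sided 5% is

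n = (z₀.₉₅ + z₀.₈₀)² × 2p(1 − p) / Δ²

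= (1.6449 + 0.8416)² × 2 × 0.96 × 0.04 / 0.07² = 6.183 × 0.0768 / 0.0049 = 96.9, so **97 per group**, as stated.

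At one-sided 0.025 the same formula gives 124. An uncorrected chi-squared equality design for 0.96 against 0.89 uses

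n = [z_α √(2p̄(1 − p̄)) + z₀.₈₀ √(p₁(1 − p₁) + p₂(1 − p₂))]² / 0.07², with p̄ = 0.925.

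- Two-sided: (1.960 × 0.3725 + 0.8416 × 0.3692)² / 0.0049 = 221.1, so 222.
- One-sided: (1.6449 × 0.3725 + 0.8416 × 0.3692)² / 0.0049 = 174.0, so 175.

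Of the designs tried, only the margin-based one at one-sided 5% gives 97.

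**2. Behaviour of the named test.** Exact enumeration over all pairs of binomial(100, p) outcomes, using the uncorrected chi-squared equality test at two-sided 0.05:

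| True regular / outpatient | p < 0.05 | of which outpatient better | p ≥ 0.05 |
|---|---|---|---|
| 0.96 / 0.96 | 4.3% | 2.1% | 95.7% |
| 0.95 / 0.95 | 4.4% | 2.2% | 95.6% |
| 0.96 / 0.89 (at the margin) | 48.1% | 0.01% | 51.9% |
| 0.95 / 0.88 (at the margin) | 44.0% | 0.01% | 56.1% |

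- If success needs p < 0.05, equal arms succeed in about 4% of trials, and half of those favour regular care. An outpatient arm 7 points worse reaches significance in 44% to 48% of trials, almost always because it is worse.
- If p ≥ 0.05 counts as success, a true 7-point deficit passes in 52% to 56% of trials.

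**3. Two single results.**

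- Regular 96/100, outpatient 90/100. Equality: z = 0.06 / √(0.93 × 0.07 × 0.02) = 1.66, p = 0.096, not significant. Against the margin: SE = √(0.96 × 0.04/100 + 0.90 × 0.10/100) = 0.0358; the one-sided 95% upper bound is 0.06 + 1.645 × 0.0358 = 11.9 points and the non-inferiority p is 0.39. Non-inferiority is clearly not shown.
- 96/100 in both arms. Equality p = 1.0. Against the margin: SE = 0.0277, upper bound 4.6 points, non-inferiority p = 0.006. Non-inferiority is clearly shown.

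Both equality p-values are non-significant, yet the correct conclusions are opposite.

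**4. Behaviour of margin-based tests.** One-sided 5%, 100 per group, exact enumeration:

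| Test | False claim at 0.95 / 0.88 | Power at 0.96 / 0.96 | Power at 0.95 / 0.95 |
|---|---|---|---|
| Farrington-Manning score | 4.9% | 74.6% | 68.2% |
| Wald, shifted by the margin | 5.9% | 80.1% | 73.0% |

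The Wald version reaches the planned power but exceeds its nominal error slightly (6.0% at 0.96 / 0.89).

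**The case against.** The strongest reply is that a margin-based test was meant all along. The hypotheses contain the margin and the chi-squared sentence follows them. The word uncorrected may refer only to continuity correction, and the square of a margin-shifted z is also referred to a chi-squared distribution on one degree of freedom. The Sample size subsection attaches the same test name to a calculation that is margin-based. Pass/fail criteria never say that a non-significant p-value means non-inferior, so the 56% belongs to a reading the protocol does not spell out. The interval method and sidedness could be left to a SAP.

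Part of this stands. The intent was probably margin-based, and the error rates above are conditional on how the p-value is read. A missing interval method alone would not be a finding. But the protocol does name a test, and by its usual meaning that test contradicts the protocol's own null. Nothing says the statistic is shifted by the margin. The extension to secondary endpoints points the other way: several secondary hypotheses in Section 5 are framed as the absence of a significant difference, which is equality testing. A SAP that follows the protocol inherits the error, and one that corrects it departs from the protocol.

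A further objection concerns power, and it also stands: a score test with 100 per group falls short of 0.80. That is a consequence to disclose, not a reason to keep a test of another hypothesis.

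**Conclusion.** The concern holds and must be fixed. In its standard meaning, the named test cannot support the pass/fail conclusion. With 100 per group, requiring significance passes a truly equal pathway in about 4% of trials. Reading non-significance as success passes a pathway at the 7-point margin in 52% (0.96 / 0.89) to 56% (0.95 / 0.88) of trials, against an intended 5%. These figures assume the usual two-sided equality test, independent binomial outcomes and complete data on 100 patients per group. The defect lies in the test specification: the 97 per group is correct for the margin-based Wald-type formula at one-sided 5%.

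**What to change.** In Section 7, Statistical design, replace the chi-squared sentence and the final-analysis p-value rule with text such as:

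> *Non-inferiority is tested by a one-sided 5% score (Farrington-Manning) test of H0: p_regular − p_outpatient ≥ 0.07. It is concluded if the upper limit of the matching two-sided 90% score confidence interval for p_regular − p_outpatient is below 7 percentage points. A p-value for equality plays no role in this conclusion.*

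Another margin-based test would also remove the contradiction, provided it is named and its error rate at the margin is shown. One-sided 5% is the level the sample size implies; one-sided 2.5% would need 124 per group by the protocol's own formula.

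In the same amendment, correct the test name under Sample size, state which test and sidedness the interim level of 0.025 applies to, and align any SAP.

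The correction costs wording only and needs no new data. The sponsor should, however, restate power for the chosen test: with the score test at 100 per group it is 74.6% at the planning value of 0.96 and 68.2% at 0.95, against the stated 0.80. Whether to accept that or enlarge the trial is a separate decision.

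### The named primary test, an uncorrected chi-squared judged at p = 0.05, tests for zero difference and contains no 7-point margin, so it cannot decide non-inferiority as the protocol defines it.

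*Protocol*

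**What the plan says.** In section 7, Statistical design, the protocol introduces its hypotheses with "We set the following null and alternative hypotheses for proving non-inferiority". The null is p_regular − p_outpatient ≥ Δ and the alternative is p_regular − p_outpatient < Δ. Here p is the proportion of patients with textbook outcome (none of the listed events within 30 days), and Δ is 7%, a margin "which is deemed clinically significant by the Principal Investigator".

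The same paragraph then names the test and its threshold: "We will use an uncorrected chi-squared statistic", and "Based on the sample size calculation done below an p value of 0.05 will be considered statistically significant". For the interim analysis, "a p value of 0.025 will be considered statistically significant". It extends the same statistic to the secondary endpoints where suitable.

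Under Sample size, power 0.80, α 0.05, a margin of 0.07 and an expected proportion of 0.96 are listed, and "this resulted in a sample size of 97 (we choose 100) patients per group when using an uncorrected chi-squared statistic".

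Under Pass/fail criteria, success requires that "the non-inferiority of outpatient recovery compared to regular treatment for bariatric surgery can be concluded". No rule for reaching that conclusion is added. Nowhere does the protocol say that the statistic is computed against a 7-point null, and it names no confidence interval to set against the margin.

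**The concern.** The uncorrected (Pearson) chi-squared of a two-by-two table has equality of the two proportions as its null hypothesis. The hypotheses in Statistical design are centred on a difference of 7 points. The protocol thus pairs a margin hypothesis with a test that has no margin in it.

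This is not a question of one side or two. The test is centred on the wrong value, and neither way of reading its p value helps. A small p value says that the groups differ, possibly because outpatients did worse. A large p value says only that a difference was not detected, which at 100 per group is weak evidence that the outpatient path is less than 7 points worse.

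At stake is the trial's one primary conclusion, whether same-day discharge after bariatric surgery is acceptable. Applied literally, the rule would either fail almost every trial in which the two paths are equally good, or pass about half of those in which the outpatient path sits exactly at the margin.

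**Working it through.** **Inputs.** From Statistical design: margin 0.07 on the risk difference, threshold 0.05, current-practice textbook outcome 95%. From Sample size: power 0.80, α 0.05, expected proportion 0.96 (taken as equal in both groups), 97 per group with 100 chosen. From section 6.1: equal group sizes.

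**1. The protocol's sample size.** The margin-based formula with equal proportions and one-sided α is

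n = 2p(1 − p)(z₀.₉₅ + z₀.₈₀)² / Δ² = 2 × 0.96 × 0.04 × (1.645 + 0.842)² / 0.07² = 96.9, so 97 per group.

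This matches the protocol. With one-sided 0.025 the same formula gives 124, so the 0.05 behind the 97 is one-sided. An equality chi-squared for 0.96 v 0.89 uses

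n = [z_α√(2p̄(1 − p̄)) + z_β√(p₁(1 − p₁) + p₂(1 − p₂))]² / (p₁ − p₂)², with p̄ = 0.925,

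and gives 174.02 (175 per group) one-sided or 221.07 (222 per group) two-sided. These two figures show only that an equality chi-squared did not produce the 97.

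**2. What the named statistic does.** With n per group,

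X² = (p̂_regular − p̂_outpatient)² / [2p̄(1 − p̄)/n],

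which contains no Δ. At 100 per group it compares with a margin-based score bound (one-sided 95% upper bound of p_regular − p_outpatient) as follows:

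| Failures, regular v outpatient | X² | Chi-squared p | Score upper bound | Against the 7-point margin |
|---|---|---|---|---|
| 4 v 4 | 0 | 1.0 | about 5.1 points | non-inferior |
| 5 v 12 | 0.0049/0.0015555 = 3.15 | 0.076 | about 14.0 points | not non-inferior |

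Both tables are non-significant, yet one shows non-inferiority and the other does not. Conversely, 3 v 10 failures gives X² = 0.0049/0.0012155 = 4.03 and p = 0.045: significant, with outpatients 7 points worse.

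**3. How often each reading goes wrong.** Exact binomial enumeration, 100 per group:

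| True rates, regular v outpatient | Chi-squared p < 0.05 | Chi-squared p ≥ 0.05 |
|---|---|---|
| 96% v 96% | 4.3% (2.1% favouring outpatients) | 95.7% |
| 96% v 89% (at the margin) | 48.1% | 51.9% |
| 95% v 88% (at the margin) | 44.0% | 56.0% |

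If p < 0.05 means success, equal groups succeed in 4.3% of trials at most, against a planned 80%. If p ≥ 0.05 means non-inferior, the false-pass rate at the margin is 52% to 56%, against 5%.

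**4. What a margin-based test does.** At 100 per group, exact results are:

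| Test of a 7-point difference, one-sided 0.05 | False-pass rate, 96% v 89% | False-pass rate, 95% v 88% | Power, both 96% |
|---|---|---|---|
| Simple z-test | 6.0% | 5.9% | 80.1% |
| Score test (Farrington-Manning) | 4.8% | 4.9% | 74.6% |

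The z-test gives these same figures whether its variance is pooled or unpooled.

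**The case against.** The strongest reply is that the authors meant a chi-squared-type statistic computed against a margin-shifted null. The hypotheses with the margin stand directly before the test. The sample size paragraph names the margin and the chi-squared together. Success is worded as a conclusion of non-inferiority, not as a p value above or below 0.05. The 97 is also compatible with such a statistic: at equal proportions pooled and unpooled variances coincide, so the number does not identify the variance form.

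Part of this stands. The intent was plainly non-inferiority, and the protocol states neither of the two literal readings as its success rule. The 4.3% and the 52% to 56% are therefore consequences of applying the wording as written, not rules that the protocol announces. But no sentence shifts the null. Using the same statistic for secondary endpoints, several of which are framed in section 5 as no difference between groups, points towards the ordinary test of equality.

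A second reply is that an unseen statistical analysis plan would settle the matter. The protocol did not leave it open: it fixed both the test and the threshold. A margin-based test in an analysis plan would contradict it.

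A reader might also infer from the 175 and 222 per group that the trial is undersized. The documents do not support that. The 97 follows exactly from the right kind of formula for the stated hypotheses and inputs.

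**Conclusion.** The rule is wrong as written. The protocol states margin hypotheses and then fixes a deciding test that has no margin, and it offers no interval or other rule in its place. This must be corrected, because the primary conclusion rests on it.

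The defect lies in the stated analysis and in one label. It does not reach the 97 per group, and mending it does not by itself call for more patients: a margin-based simple z-test at 100 per group has 80.1% exact power if both true rates are 96%. Any fall to about 75% would come from choosing a score method, not from the correction.

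The error rates assume 100 analysed patients per group, independent binomial outcomes, a single final analysis and the true rates shown. Whether 96% is the right planning rate, when current practice is given as 95%, is a separate question.

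**What to change.** In Statistical design, replace the chi-squared for the primary endpoint by a one-sided 0.05 test of the null that p_regular − p_outpatient equals 7 points. Equivalently, state that non-inferiority is concluded only if the one-sided 95% upper bound of that difference is below 7 points. Say that the 0.05 is one-sided. If the interim threshold of 0.025 is meant for the same hypotheses, say there too that the p value comes from the margin-based test. Refer to this rule under Pass/fail criteria.

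In Sample size, name the margin-based one-sided formula in place of the chi-squared label.

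Any test or interval that contains the margin cures the defect. A score method (Farrington-Manning test or Miettinen-Nurminen interval) is the better calibrated option, with an exact false-pass rate of 4.8% to 4.9% against about 6% for the simple z-test. If it is chosen, restate the power at 96% and 100 per group as about 75% instead of 80%.

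The cost is a few sentences in an amendment. The endpoint, the margin and the planned 100 per group need not change.

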### Interim analysis

The interim analysis will take place when data from 50 patients in both groups has been collected. Interim analysis will involve a comparison of the textbook outcome, as described above for the primary endpoint, between the two groups. The individual parameters of the textbook outcome will also be compared, i.e. discharge as planned, readmission in the 30 days after surgery, additional consultation by phone in the 7 days after surgery, additional consultation in the 7 days after surgery, and patient satisfaction. Based on the outcome of this interim analysis the investigators together with the sponsor will decide if the study needs to be stopped.

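### The interim level of 0.025 is called an alpha correction, but the final test keeps the full one-sided 0.05, so the two levels do not form a valid correction

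*Protocol*

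**What the plan says.** All of this is in section 7 of the protocol unless noted.

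- **Hypotheses (Statistical design).** The only pair set out is the non-inferiority pair, introduced by "We set the following null and alternative hypotheses for proving non-inferiority". The null is that the textbook-outcome proportion is worse by at least 7 points in the outpatient group. A small p value therefore supports non-inferiority.
- **Final level (Statistical design).** "Based on the sample size calculation done below an p value of 0.05 will be considered statistically significant".
- **Interim level (Statistical design).** "For the interim analysis an alpha correction for multiple testings is applied and a p value of 0.025 will be considered statistically significant".
- **Sample size.** The calculation assumes a textbook-outcome proportion of 0.96 and a 7-point margin, at alpha 0.05 and 80% power. Its outcome is given as follows: "this resulted in a sample size of 97 (we choose 100) patients per group when using an uncorrected chi-squared statistic".
- **Interim analysis.** It takes place at 50 patients in both groups, and "Interim analysis will involve a comparison of the textbook outcome, as described above for the primary endpoint, between the two groups". The investigators and the sponsor then decide whether the study must stop.
- **Termination on statistical grounds.** The only reasons listed are unacceptable inferiority and an unanticipated accumulation of adverse events.
- **Pass/fail criteria.** "The study is considered successful if the primary endpoint is addressed" and non-inferiority can be concluded. The text does not say at which analysis.
- **Section 1, Milestones.** The interim is listed as after 50 patients, which can be read as 50 in total.

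**The concern.** A correction for multiple testing has to limit all looks together to the nominal level. Here the first look receives 0.025 and the last look still receives the whole 0.05. If either look can yield a positive conclusion, the total must exceed 0.05.

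A false positive in this trial means concluding that same-day discharge is non-inferior when the textbook outcome is in truth at least 7 points worse. The section on claims in chapter 5 says that claims may be derived from the primary hypothesis. The people who see the interim comparison also decide on stopping, so the meaning of an interim p below 0.025 should be fixed beforehand. The protocol states both levels itself and calls one of them a correction, so this is not a detail left to a later analysis plan.

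**Working it through.** **Step 1. Reproduce the sample size, to settle what 0.05 means.** Inputs from the Sample size paragraph: proportion 0.96 (taken as equal in both groups), margin 0.07, power 0.80, alpha 0.05.

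n per group = (z₁₋α + z₀.₈₀)² × 2p(1−p) / Δ²

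- One-sided 0.05: (1.645 + 0.842)² × 2 × 0.96 × 0.04 / 0.07² = 6.183 × 0.0768 / 0.0049 = 96.9, so 97. This matches the plan.
- One-sided 0.025: 124. This does not match.

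The 0.05 is therefore one-sided, and all of it is used at the final test.

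**Step 2. If an interim p below 0.025 may count as non-inferiority.** Take both levels as one-sided, with the true difference at the margin. Let Z₁ and Z₂ be the interim and final statistics, standard bivariate normal with correlation equal to the square root of the information fraction. The boundaries are 1.960 (level 0.025) and 1.645 (level 0.05).

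Overall error = 1 − P(Z₁ < 1.960, Z₂ < 1.645)

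| Interim timing | Information fraction | Correlation | Overall one-sided error |
|---|---|---|---|
| 50 per group (Interim analysis) | 50/100 = 0.50 | 0.707 | 0.0625 |
| 50 in total, 25 per group (one reading of Milestones) | 25/100 = 0.25 | 0.500 | 0.0676 |

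The excess over 0.05 is about 1.2 or 1.8 percentage points. It consists of trials that cross at the interim but would fail the final test. The crude ceiling is 0.025 + 0.05 = 0.075.

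**Step 3. If the interim serves only to stop for inferiority or adverse events.** Non-inferiority can then be declared only at the final look. Stopping for harm can only remove chances to declare it, so the nominal error stays at or below 0.05 and no correction is needed. The interim level does not serve this purpose either: under the stated hypotheses a p below 0.025 is evidence for non-inferiority, whereas the termination paragraph is concerned with inferiority. The level would then have no function for the stated stopping decision, but the text would still call such an interim result significant.

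**Step 4. Set the two readings together.** Under the first, the correction does not hold 5%. Under the second, it is not needed and is attached to the wrong question. The sentence needs an edit either way.

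**The case against.** The strongest reply is that the passages governing the use of the interim point away from any early claim. The interim paragraph speaks only of deciding whether to stop, and the termination paragraph names only inferiority and adverse events. Neither provides for stopping because non-inferiority has been shown. The final level is tied to the sample size calculation, which is the full-sample test. The pass rule is silent on timing, and silence is not permission to claim at the interim.

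Most of this stands. A reader might infer from the two levels that the trial runs at a 6.2% error rate. The documents do not support that as a certainty, because no passage describes an interim non-inferiority conclusion. It would also be wrong to say that a stated figure is miscalculated: the sample size reproduces exactly.

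The reply does not rescue the sentence. If the interim cannot support non-inferiority, there is nothing for an alpha correction to correct. If 0.025 was meant as a threshold for harm, the protocol does not say so, and it sets out no hypothesis for which a small p value would indicate harm.

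**Conclusion.** The concern holds as a mismatch between two stated levels and an unstated role for the interim p value. The overall one-sided error is about 6.2% (interim at 50 per group) to 6.8% (50 in total), but only if an interim p below 0.025 may count as non-inferiority. If the interim is for harm only, which the termination paragraph favours, the inflation is nil and the defect is a significance level without a function.

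The figures assume one-sided tests at both looks, equal groups, 100 per group at the end and a large-sample normal approximation. With proportions near 0.95 and 50 to 100 patients per group, the true error of a particular test may differ from its nominal level. That is a separate matter and should not be added to the size of this defect.

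The point should be corrected before the interim, because it concerns error control for the primary conclusion.

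**What to change.** In section 7, Statistical design and Interim analysis:

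1. State that non-inferiority can be concluded only at the final analysis, at one-sided 0.05.
2. State that the interim serves only the stopping reasons already listed under termination on statistical grounds.
3. Delete the interim 0.025 significance level for non-inferiority, together with its description as an alpha correction.

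This is a text change. It costs no power and no patients: 100 per group at one-sided 0.05 keeps about 81% power under the plan's own assumptions.

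Keeping an early non-inferiority claim and lowering the final level is not a cost-free alternative. With 0.025 at an interim of 50 per group, the final level that restores 5% in the normal approximation is about 0.035. Power of the final test at 100 per group is then Φ(0.07 / √(2 × 0.96 × 0.04 / 100) − 1.807) = Φ(2.526 − 1.807), about 76%, or about 78% counting both looks. Both are below the stated 80%, and the fixed-sample formula then asks for 110 per group.
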